## Methods

### Trial design

The MATISSE study (Multi-centre study of Art Therapy In Schizophrenia - Systematic Evaluation) is a three-arm, parallel group, pragmatic, randomised, controlled trial of referral to group Art Therapy plus standard care, referral to an attention control 'activity' group plus standard care, or standard care alone. Similar numbers of participants were randomised to each of the three arms of the trial. We aimed to use a pragmatic design which would allow us to test the impact of referring people to group Art Therapy in normal clinical practice.

Three changes were made to the design of the study after commencement. Firstly, because recruitment was slower than anticipated the period for recruiting the study sample was increased from nine to 20 months [18]. Secondly, following publication of national guidance on the treatment of schizophrenia highlighting the importance of arts therapies in treating symptoms of schizophrenia [19], we promoted total symptom score as a co-primary outcome measure. Finally, early data demonstrating lower levels of attendance at groups than we anticipated led us to increase the total number of participants to 10% above our original target. Ethical approval for the study, including these protocol amendments, was given by Huntingdon Research Ethics Committee (06/Q0104/82) and the study protocol was registered with Controlled Clinical Trials (ISRCTN46150447) prior to the start of data collection.

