#### Standard care

Standard care involved follow-up from secondary care mental health services, care coordination, pharmacotherapy and the option of referral to other services. No restrictions were imposed on referral to other services apart from arts therapies which participants agreed not to use until the final follow-up assessment had been completed.

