### Study procedures

In each centre researchers publicised the study through meetings with staff at local inpatient units, community teams, day centres and residential units. Researchers visited these teams on a regular basis to remind staff about the study and promote recruitment of potential participants. Researchers were assisted in this by clinical studies officers of the UK Mental Health Research Network. Clinical staff were given a copy of an information sheet which summarised the study protocol and helped them identify patients who may be suitable for the study. Researchers met those who had given verbal consent to be approached about the study, assessed eligibility, provided written and verbal information, obtained written consent, and collected baseline data. Participants were then randomised via an independent remote telephone randomisation service using permuted stacked blocks, stratified by site. The block size was randomly assigned between three and six. Each element within the block was randomly assigned to one of the three treatments in proportion to the size of the block.

Participants, their key worker and their general practitioner were notified of allocation status by an independent administrator. The administrator simultaneously informed local art therapists or activity group facilitators of the allocation status of the participant so that arrangements could be made for the participant to receive their allocated intervention while researchers involved in collecting follow-up data remained masked.

Rater 'masking' was maintained by providing specific instructions to participants and their clinical teams not to disclose treatment details. Data are held securely and all personal identifiers removed, with randomisation details held separately and password protected. Data on participants' uptake of the trial interventions was monitored through proforma completed by group facilitators after each group as described above. Thus researchers did not have to record this information from case files as this would have led to unmasking. Participants completing follow-up interviews were offered a £15 honorarium in recognition of their time in completing research interviews and any inconvenience related to their involvement in the study.

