### Statistical analysis

All primary statistical analysis will use the intention-to-treat principle. The statistical package STATA (version 11.0) will be used for all the analyses. The numbers (with percentages) of losses to follow-up at 12, and 24 months after randomisation will be reported and compared between the treatment arms with absolute risk differences (95% Confidence Intervals); any deaths and their causes will be reported separately.

For our main analysis we will impute baseline missing covariates using either mean or regression imputation to increase power and precision of the estimated treatment effect [36]. We will use all available results without imputation of missing outcomes. For the continuous outcomes, differences in mean score between those randomised to each of the three arms of the trial will be examined using analysis of covariance adjusting by 1) site and baseline value of outcome 2) site, baseline value of the outcome, sex and age. The assumption of linearity will be assessed by residual analysis; if necessary bootstrapping techniques will be employed.

Two sensitivity analyses will be conducted to take into account missing data 1) multiple imputation, which assumes data are 'missing at random', and 2) replacement of the missing GAF scores with those from the GAF proxy measure that we collected from participants' key workers.

We anticipate that there will be clustering of outcomes as a result of patients being assigned to groups facilitated by different therapists in different sites. Such clustering violates the assumption that observed outcomes of individuals are independent and can result in increased standard errors [37,38]. To take account of this we will explore separately therapist and site as random effects and finally a three-level model will be fitted, with patients as level one, therapist as second level, and the site as the third level. If our conclusions depend on which model is adopted we will present all results in the principal paper.

In a secondary analysis we will examine the impact of the level of uptake of groups using Complier Average Causal Effect analysis [39]. Instrumental variable methods will be used to model our outcome adjusting for age and sex. Randomisation allocation will be used as an instrumental variable.

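### The secondary complier-average (CACE) analysis is stated to adjust for age and sex, leaving out the site and baseline score that both main models include, at a cost in precision

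*Protocol article*

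**What the plan says.** The Statistical analysis section of the protocol article describes the uptake analysis in three sentences: "In a secondary analysis we will examine the impact of the level of uptake of groups using Complier Average Causal Effect analysis"; "Instrumental variable methods will be used to model our outcome adjusting for age and sex"; and "Randomisation allocation will be used as an instrumental variable".

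Earlier in the same section, the main comparison of continuous outcomes is an analysis of covariance in two versions, "adjusting by 1) site and baseline value of outcome 2) site, baseline value of the outcome, sex and age". Site and baseline are therefore in both versions, and sex and age enter only in the second. The section also plans to impute missing baseline covariates, giving power and precision as the reason.

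Study procedures states that patients were allocated "using permuted stacked blocks, stratified by site". Trial design describes three arms: "Similar numbers of participants were randomised to each of the three arms of the trial". The Measures section has each outcome measured at recruitment as well as at one and two years. The article mentions a full statistical analysis plan, which is not shown.

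**The concern.** The CACE sentence names its covariates, so this is a stated choice and not a detail left open. The named set keeps the two covariates that the main analysis treats as additional and drops the two that it treats as core. One of the dropped covariates is the stratification factor. The other, the baseline value of the same scale, would usually be expected to predict the 24-month score better than age or sex does.

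What is at stake is precision. An instrumental variable estimate has a wide interval to begin with, and leaving out a good predictor of outcome widens it further for no gain. The plan's own reason for imputing missing baseline covariates applies equally here.

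**Working it through.** **Figures in the plan.** The article gives no figure for the CACE analysis, so there is none to reproduce. Its sample size does reproduce: the t-based size for 6 points with SD 10 is 44.6, so 45 per arm; 1 + 7 × 0.175 = 2.225 (article: 2.22); 45 × 2.225 = 100.1; and 300/0.8 = 375, against 376 = 4 × 94. It does not bear on this point, except that the clustering figures are used in step 4.

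**1. Covariates side by side (Statistical analysis)**

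| Model | Site | Baseline value | Sex | Age |
|---|---|---|---|---|
| Main model 1 | yes | yes | no | no |
| Main model 2 | yes | yes | yes | yes |
| CACE | not named | not named | yes | yes |

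**2. Cost of omitting baseline.** Let r be the correlation between baseline and 24-month outcome. Adjusting for baseline multiplies the residual variance by 1 − r², so omitting it multiplies the standard error by 1/sqrt(1 − r²). The sample-size equivalent of the loss is r². The document does not give r, so a range is shown:

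- r = 0.3: 1/sqrt(0.91) = 1.048, about 5% (9% of the sample)
- r = 0.5: 1/sqrt(0.75) = 1.155, about 15% (25%)
- r = 0.7: 1/sqrt(0.51) = 1.400, about 40% (49%)

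**3. Bias or precision?** A simulation of 2,000 trials checked this by two-stage least squares. Each trial had 300 patients, three equal arms within four sites, about 58% attendance related to prognosis, a baseline–outcome correlation of about 0.5, no clustering by group, and true attendance effects of 6 (Art Therapy) and 2 (activity). Allocation entered as two indicators against standard care.

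- Adjusting for age and sex: mean estimates 5.96 and 1.94; empirical SD 2.46 for both.
- Adding baseline and site: mean estimates 5.95 and 1.92; empirical SD 2.08 and 2.05.

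The estimates hardly move. The SD falls by about 16%, which is close to step 2 at r = 0.5 with a little more from site.

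**4. Allowing for clustering.** Step 2 treats outcomes as independent. With the plan's cluster size of 8 and ICC of 0.175, the variance multiple is 2.225 in a group arm and 1 under standard care. Suppose everything that baseline explains is at patient level, so that it removes r² from each. The standard-error ratio for a group arm against standard care is then sqrt(3.225/(3.225 − 2r²)):

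- r = 0.3: sqrt(3.225/3.045) = 1.029
- r = 0.5: sqrt(3.225/2.725) = 1.088
- r = 0.7: sqrt(3.225/2.245) = 1.199

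If the analysis carries that much clustering, the cost is about 3%, 9% or 20%.

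**5. Identification.** A model with an intercept, age, sex and both attendances has five coefficients. With two allocation indicators as instruments the moment matrix has rank 5 of 5, so both attendance effects are identified. With one binary indicator the rank is 4 of 5, so they are not.

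**The case against.** The strongest defence is that this is a three-sentence summary of a secondary analysis. It does not say that only age and sex will be used, and a full analysis plan exists. The omission also causes no bias under randomised allocation, and the primary intention-to-treat analysis has the right covariates. All of this stands, and it makes the point a modest one. It does not remove it, because the article names the covariates and they differ from those of its own main models. The size is also uncertain: at r = 0.3 the loss is only about 5%.

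A reader might infer several stronger points that the document does not support.

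- **One instrument cannot separate the effects of attending two kinds of group.** The article names allocation as the instrument but never reduces it to one binary indicator. Three arms supply two indicators, which suffice (step 5). Comparing one group arm with standard care needs only one instrument for one exposure. For Art Therapy this is helped by the restriction under Standard care: "apart from arts therapies which participants agreed not to use until the final follow-up assessment had been completed".
- **The Art Therapy v activity complier effect is uninterpretable.** No such analysis is written down. Contrasts, coding of allocation and the definition of uptake are commonly left to the analysis plan. The caveat is real in general: those who attend one group need not be those who would attend the other. It applies only if that contrast is attempted.
- **The CACE and intention-to-treat estimates cannot be compared.** In a linear model under randomisation, the extra covariates change precision and not the quantity estimated.
- **Partial uptake already doubles the standard error at 50% attendance.** The estimate is divided by uptake as well, so the ratio of estimate to standard error is essentially unchanged. This is true of any CACE analysis, and the 50% is not in the document.

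**Conclusion.** The point holds as one of precision and consistency in a secondary analysis. As stated, the CACE model leaves out site and the baseline value of the outcome, which both main models include. With independent outcomes the standard error is about 5%, 15% or 40% larger for r = 0.3, 0.5 or 0.7, and less if the clustering assumed in the sample size is carried into the analysis. All of these figures rest on an assumed r and on reading the listed covariates as the full set.

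The absence of bias rests on randomised allocation. Missing outcomes are a separate matter: if drop-out depended on baseline score differently between arms, conditioning on baseline would also give some protection. The document offers no evidence either way. Nothing here affects the primary analysis.

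**What to change.** Amend the CACE sentence so that site, baseline value of the outcome, sex and age enter both stages of the instrumental variable model, matching the fuller main analysis of covariance.

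If attendance at Art Therapy and at activity groups is modelled together, enter the three-arm allocation as two indicators with standard care as reference. If a direct Art Therapy v activity complier effect is reported, state the further assumption on which it rests, such as homogeneous effects.

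The cost is wording only. Baseline scores, site, sex and age are already collected, and group attendance is recorded on the facilitators' forms.

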**Method/Design:**

The MATISSE study is a three-arm, parallel group, pragmatic, randomised, controlled trial of referral to group Art Therapy plus standard care, referral to an attention control 'activity' group plus standard care, or standard care alone. Study participants were recruited from inpatient and community-based mental health and social care services at four centres in England and Northern Ireland. Participants were aged over 18 years with a clinical diagnosis of schizophrenia, confirmed by an examination of case notes using operationalised criteria. Participants were then randomised via an independent and remote telephone randomisation service using permuted stacked blocks, stratified by site. Art Therapy and activity groups were made available to participants once a week for up to 12 months. Outcome measures were assessed by researchers masked to allocation status at 12 and 24 months after randomisation. Participants and care givers were aware which arm of the trial participants were allocated to. The primary outcomes for the study are global functioning (measured using the Global Assessment of Functioning scale) and mental health symptoms (measured using the Positive and Negative Syndrome Scale) assessed at 24 months. Secondary outcomes were assessed at 12 and 24 months and comprise levels of group attendance, social function, satisfaction with care, mental wellbeing, and costs.

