### Measures

At baseline, demographic and clinical data were collected including; age, gender, ethnicity, highest level of educational achievement, employment status, housing status, date of first presentation to clinical services with schizophrenia, primary and any secondary clinical diagnosis, current medication, and previous receipt of structured psychosocial interventions including arts therapies. Written records and in some cases collateral information gathered from carers or health professions were used to generate a psychiatric diagnosis using operationalised criteria [20]. Primary and secondary outcome measures are listed below. Each measure was assessed at recruitment (baseline), one year and two year follow-up. Measures were completed either by the researcher, the participant or by their key worker as indicated below.

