#### Completed by the researcher

i) Global functioning (co-primary outcome) - was assessed using the Global Assessment of Functioning Scale (GAF), a 100-point single item, observer-rated scale that rates functioning on a continuum from health to illness. It is a reliable and valid measure of global functioning that has been widely used in previous studies of people with schizophrenia and is sensitive to change [24].

ii) Mental health (co-primary outcome) - was assessed using the Positive and Negative Syndrome Scale [25]. This is a 30-item rating scale which is accompanied by a structured interview. It takes approximately 30 minutes to complete and has been widely used to examine changes in symptoms in people with schizophrenia and related psychoses.

iii) Medication - was recorded all medication being prescribed to participants and assessed concordance using the Morisky Scale a four item questionnaire which provides a valid estimate of use of psychotropic medication [26].

iv) Health related quality of life - was assessed using Euroqol EQ-5 D [27]. This is a generic measure for describing and valuing health-related quality of life assessed in five domains (mobility, self-care, usual activities, pain/discomfort, anxiety/depression).

v) Cost data - was assessed using a modified version of the Adult Service Use Inventory which was designed on the basis of previous studies in adult mental health populations [28,29] and adapted for the purpose of this study.

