### Sample size

The sample size calculation for the study was based on the primary hypothesis: that those referred to group Art Therapy will have improved global functioning at 24 months compared to those referred to attention control treatment or standard care alone. Global functioning had not been assessed in randomised trials of Art Therapy for people with schizophrenia that had been completed when the study was being planned, so data on mean GAF scores and standard deviations were taken from previous trials of Compliance Therapy and Cognitive Therapy for people with schizophrenia. These interventions demonstrate an improvement in GAF scores of between five and 10 points [16,17]. We powered this trial to be able to detect a difference in GAF score of six points.

To detect a mean difference in global functioning of six points on the GAF (SD = 10.0) at 24 months with a two-sided significance level (α) of 5% and power of 80% would require 45 patients in each arm of the trial. In trials of complex interventions there is likely to be clustering of the intervention effect within therapists. In our recent trial of music therapy for people with schizophrenia we observed an intra-class correlation coefficient (ICC) of 0.125 [35]. However we anticipated that group processes may lead to a greater clustering of effects and decided to use an ICC of 0.175 for this trial. With an estimated cluster size of 8 and an ICC of 0.175 the Design Effect for the trial is 2.22 and a sample size of 100 per group was therefore required. A sample of 100 participants in each of the three arms of the trial would be sufficient to detect a difference of 50% in mean costs, at the 5% level of significance and with 80% power. In anticipation of a 20% loss to follow up at 24 months, we planned to randomise 376 participants, 94 at each centre.

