The health economic evaluation will be conducted from the societal perspective, covering services received and any productivity losses. Differences in mean costs will be analysed using standard parametric t-tests with the validity of results confirmed using bias-corrected, nonparametric bootstrapping (repeat re-sampling) [40]. Despite the skewed nature of cost data, this approach is recommended to enable inferences to be made about the arithmetic mean [41]. In a secondary analysis, cost-effectiveness will be assessed through the calculation of incremental cost-effectiveness ratios [42] and will be explored in terms of global functioning (primary analysis) and quality adjusted life years using the EQ-5 D measure of health-related quality of life. Uncertainty around the cost and effectiveness estimates will be represented by cost-effectiveness acceptability curves [43].

A full Statistical Analysis Plan was developed by the team and ratified by an independent Trial Steering Group prior to data analysis.

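### Mean costs are compared by an unadjusted t-test although service use is collected at baseline and the plan adjusts its other continuous outcomes, so the cost comparison is less precise than it need be

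*Protocol article*

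**What the plan says.** The health economic paragraph of Statistical analysis fixes the cost comparison: "Differences in mean costs will be analysed using standard parametric t-tests with the validity of results confirmed using bias-corrected, nonparametric bootstrapping". The reason given is that this permits inference on the arithmetic mean despite skewness. No covariate, site term or cluster term is mentioned.

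Other parts of the article bear on this choice:

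- Measures, on the listed instruments: "Each measure was assessed at recruitment (baseline), one year and two year follow-up". The list that follows includes service use ("Cost data - was assessed using a modified version of the Adult Service Use Inventory").
- The abstract counts costs among the outcomes: "Secondary outcomes were assessed at 12 and 24 months and comprise levels of group attendance, social function, satisfaction with care, mental wellbeing, and costs".
- Study procedures stratifies randomisation by site.
- Statistical analysis compares continuous outcomes by "analysis of covariance adjusting by 1) site and baseline value of outcome 2) site, baseline value of the outcome, sex and age". On therapist groups it says: "Such clustering violates the assumption that observed outcomes of individuals are independent and can result in increased standard errors".
- Sample size makes a power claim for mean cost, with 5% significance and 80% power: "A sample of 100 participants in each of the three arms of the trial would be sufficient to detect a difference of 50% in mean". No standard deviation or coefficient of variation is given.

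**The concern.** The article sets one rule for its continuous outcomes and a weaker one for costs, without saying why. A standard two-sample t-test discards the baseline service-use data, ignores the stratification factor and treats patients as independent.

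The stated reason, inference on the arithmetic mean, argues against log transformation or rank tests. It does not argue against covariates, because a linear regression coefficient for arm is also a difference in arithmetic means.

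Cost-effectiveness is hypothesis (ii) under Research objectives. At stake are the width of the interval for the cost difference, any chance imbalance left in the estimate and, if costs cluster within groups, the honesty of that interval.

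**Working it through.** **Step 1. The plan's own figures.** Inputs from Sample size: difference 6, SD 10, two-sided 5%, power 80%, cluster size 8, ICC 0.175, 20% loss.

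- Per arm before clustering: 2 × (1.96 + 0.842)² × (10/6)² gives 44 by the normal approximation; the t-based value is 44.6, rounded up to 45. Reproduced.
- Design effect: 1 + 7 × 0.175 = 2.225; 45 × 2.225 = 100.1. Reproduced.
- Total: 3 × 100 / 0.8 = 375, against 376 = 4 × 94. Reproduced.

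The cost power claim cannot be reproduced, because no coefficient of variation (CV, SD divided by mean) is stated. Solving backwards, the largest CV compatible with it is 0.5 / [(1.96 + 0.842) × √(2/100)] = 0.5 / 0.396 = 1.26 without clustering.

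**Step 2. Precision lost by not adjusting.** With correlation r between baseline and follow-up cost, adjustment multiplies the variance by 1 − r². The SE falls by 1 − √(1 − r²), and the gain equals 1/(1 − r²) − 1 more patients. The values of r are assumptions. The last two columns also assume 100 per arm and CV 1.26, where the unadjusted test has 80% power for a 50% difference.

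| r (assumed) | Fall in SE | Equivalent extra patients | Power for 50% difference | Detectable at 80% power |
|---|---|---|---|---|
| 0.3 | 5% | 10% | 84% | 48% |
| 0.5 | 13% | 33% | 90% | 43% |
| 0.6 | 20% | 56% | 94% | 40% |

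**Step 3. Chance imbalance.** With 100 per arm, the SE of the standardised baseline difference is √(2/100) = 0.141. A one-SE imbalance moves the unadjusted cost difference by r × 0.141 × CV. At CV 1.26 this is about 5%, 9% or 11% of mean cost for r = 0.3, 0.5 or 0.6. Adjustment removes this shift.

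**Step 4. Clustering, if present in costs.** With 8 per group, the variance factor is 1 + 7 × ICC for Art Therapy against the activity group. Standard care has no groups, so for a group arm against standard care the factor is the average of that value and 1. The cost ICC is assumed. The values 0.125 and 0.175 are those that Sample size cites from a music therapy trial and assumes for this one.

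| Cost ICC (assumed) | True SE / t-test SE, both arms grouped | Type I error of nominal 5% test | True SE / t-test SE, one arm grouped | Type I error of nominal 5% test |
|---|---|---|---|---|
| 0 | 1.00 | 5% | 1.00 | 5% |
| 0.05 | 1.16 | 9% | 1.08 | 7% |
| 0.125 | 1.37 | 15% | 1.20 | 10% |
| 0.175 | 1.49 | 19% | 1.27 | 12% |

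If the ICC of 0.175 held for costs, the CV limit in Step 1 would fall from 1.26 to 1.26/√2.225 = 0.85 between the two group arms, and to 1.26/√1.6125 = 0.99 for a group arm against standard care.

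**The case against.** The strongest reply is that nothing here is biased. Randomisation makes the unadjusted difference valid, the article gives a reason for its method, and costs are a secondary outcome. That stands, and it limits the point to efficiency and chance imbalance.

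Further objections, and what remains of each:

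- **The correlations are assumed.** They are. Inpatient details were also drawn from records for the two years before the end of follow-up, and no matching look-back before baseline is described. The baseline cost may therefore not be like for like, and r may be low. The gain would then be small, but adjustment would still cost almost nothing.
- **Costs may not cluster.** The ICC of 0.175 was chosen for global functioning, and attendance was lower than expected. This stands, so clustering remains conditional.
- **The analysis plan may add adjusted models.** It may. But the article does not leave the method open; it names the t-test. If the adjustment rule for continuous outcomes was meant to cover costs, the two statements need reconciling.

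Three stronger readings are tempting but not supported:

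- A reader might infer that quality-adjusted life years are also unadjusted. The article says only that they use the EQ-5D. It does not say how they are built, and the adjustment rule for continuous outcomes may cover them.
- A reader might infer that unit costs differ between sites. The article describes a mix of areas and populations, not prices.
- A reader might infer that the bootstrap intervals or acceptability curves are too narrow. The resampling unit is not stated, and the article does not say that the t-test result feeds the curves.

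**Conclusion.** The point holds for the cost comparison. The article fixes an unadjusted analysis although it has the baseline data and adjusts its other continuous outcomes. The demonstrated harm is lost precision and uncorrected chance imbalance, not bias. The size depends on an unstated correlation: an SE reduction of about 5% to 20% for r between 0.3 and 0.6.

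Understated uncertainty from clustering is a conditional addition. It rests on the article's own statement about non-independence and on a cost ICC that the article does not give. The effect would be largest for Art Therapy against the activity group and smaller against standard care. The change is worth making before analysis, but the planned comparison is not invalid without it.

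**What to change.** - **Main analysis:** linear regression of total cost on arm, site and baseline cost, with bootstrap intervals. This keeps the difference in arithmetic means as the target. The article's rule for imputing missing baseline covariates can be applied to baseline cost.
- **Cost-effectiveness:** use the same adjusted cost difference in the incremental ratios and acceptability curves, and say so.
- **Sensitivity analyses:** keep the unadjusted t-test. Also fit the therapist random-effects model from Statistical analysis to costs, with clustering in the two group arms only. Define the cluster as the group to which the participant was referred, since members left, were replaced or did not engage.
- **Avoid** a bootstrap of whole groups within arm-by-site strata. With 100 to 139 per arm (417/3 = 139), four sites and 8 per group, each stratum has about 3 to 4 groups (100/32 = 3.1; 139/32 = 4.3). Uncorrected resampling of m groups gives SEs too small by about 1 − √(1 − 1/m), which is 18% at m = 3 and 13% at m = 4. That is similar to the 14% error (1 − 1/1.16) of ignoring a cost ICC of 0.05 between the two group arms.

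The cost is plan wording, some extra code and a rule for assigning participants to groups. No new data are needed.
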